**EMDR Recent-Traumatic Events Protocol:**

In patients who have experienced critical illness the traumatic episode can be regarded as the continuum of all that has happened from the initial traumatic event, until the present day covering the entirety of the ICU admission, up to the point of therapy.

Systematic reviews suggest that earlier interventions appeared to be more effective at preventing long-term psychological symptoms before they become entrenched[24, 69]. The POPPI study which examined delivering psychological support to the patient whilst still being care for within the ICU did not show benefit. It is suggested that the intervention may have been too early with the patients being too ill and fatigued to implement some of the suggested behavioural strategies [54].

The EMDR Recent Traumatic Events Protocol (R-TEP) is designed to be delivered soon after the traumatic event, in order to promote memory processing that will be preventative against longer-term psychological symptoms[70]. EMDR R-TEP conceptualises the memories as unprocessed experiences which are still fragmented due to the recent and potentially ongoing nature of the trauma.

In 2018, Gil-Jardine et al reported that an EMDR R-TEP intervention, delivered in the Emergency Room, for patients presenting with a medical or traumatic event, reduced incidence of PTSD at 3-months. PTSD symptoms were experienced by 3% of patients who had received EMDR R-TEP compared with 19% of the patients who did not receive EMDR R-TEP [71]. EMDR R-TEP has not been used in patients at risk of PTSD following critical illness.

**Online psychological care:**

Social distancing guidelines and the potentially long-term nature of the Covid-19 epidemic require the adoption and robust testing of technological solutions, in order to assure access to best possible psychological care.

The American Psychiatric Association Donald M. Hilty, 2020 #568} and the British Psychological Society[72] support online videoconferencing to offer psychological support, based on considerations of safety, increased access and effectiveness [73] .

Our psychology team are already delivering EMDR R-TEP online. This approach is supported by the NHS digital arm NHSx.[74]

1. **Aims**

## Primary aim:

This is a feasibility study to test whether an early online EMDR R-TEP intervention, can be delivered, starting within 12-weeks following hospital discharge, for adult survivors of Covid-19 related critical illness.

## Secondary objectives: To investigate whether online EMDR R-TEP affects

1. Psychological symptoms
2. Quality of life
3. Cognitive function
4. Physical activity
5. Nutritional status

A subsequent process evaluation will be conducted to assess therapeutic adherence to the EMDR protocol and to gather opinion and evidence of participants. Our results, will inform the design of a future randomised-controlled trial to test the effectiveness of the online EMDR R-TEP intervention in ameliorating psychological problems for adult survivors of Covid-19 related critical illness.

# **Figure 1: Trial patient flow**

[figure not shown]

1. **Method**
   1. ***Trial Design and setting***

This is a single-centre, randomised controlled feasibility cohort trial.

Patients will be recruited from University Hospital Southampton Intensive Care Unit on the south coast of the United Kingdom.

Consenting participants will be referred to IPTS, Branksome Clinic, a community-based, NHS specialist therapy support unit, for people with emotional and psychological health problems.

- 1. ***Patient eligibility***

**Inclusion Criteria:**

Acute admission to Critical Care who have required mechanical ventilation for at least 24 hours

Covid-19 positive by PCR

>18 years of age

Capacity to provide informed consent and to complete trial interventions and assessments.

**Exclusion criteria:**

Pre-existing cognitive impairment such as dementia

Pre-existing psychotic diagnosis

Not expected to survive post-hospital discharge

- 1. ***Recruitment and consent process***

Hospital research staff will screen all patients within the Intensive Care Unit (ICU). Patients who fulfil the inclusion criteria and have none of the exclusion criteria will be approached to discuss trial participation either within the hospital or within 12-weeks of hospital discharge. Capacity to consent must be determined in accordance to the Mental Capacity Act 2005.

In-hospital approach: The initial conversation can be made face-to-face within the hospital. The patient will be given the Patient Information Sheet and adequate time to consider participation according to Good Clinical Practice guidelines.

Prior to hospital discharge, hospital research staff, with delegated duty of consent, will ask the patient to consider signing an informed consent form provided by the trial.

Post-hospital discharge approach: If the patient has been discharged from hospital, within the last 12-weeks, research staff will make initial contact with a telephone call. If the patient expresses an interest, research staff will post or email the study Patient Information Sheet. A follow-up phone call will be arranged. If the patient expresses a desire to participate in the study, the research staff will document the conversation and sign a consent form on behalf of the patient. A copy of the consent form will be posted to the patient.

- 1. ***Patient randomisation***

Consenting participants will be randomly allocated to intervention or usual care using an internet based system. Participants will be randomly assigned to receive either standard care (control) or the standard care plus online EMDR R-TEP (Intervention) [70]

- 1. ***Intervention***

Group one: patients in the control arm will receive their standard package of prescribed care, following discharge home from hospital. If they experience any adverse physical or psychological health-conditions they will access care through the usual available channels.

Group two: patients in the intervention arm will receive their standard package of prescribed care, following discharge home from hospital. In addition they will be referred to the Intensive Psychology Therapy Service. They will receive an initial online appointment within 12-weeks of discharge home from hospital. Their assigned psychological therapist will introduce the therapy and assess their distress using the 'Subjective Units of Distress' tool. Patients rate their distress on a scale from 0 (no anxiety at all) to 10 (unbearably bad).

The therapist will then ask the patient to recount the story of their Intensive Care stay, while watching the therapist's finger-movements or tapping, in a side-to-side motion. The science behind this is not fully understood, but it is believed to help patients to mentally process traumatic events, while remaining calm. Traumatic events negatively affect people, in the long-term, when memories of them have not been fully or effectively processed.

Following the online EMDR R-TEP sessions, the therapist will repeat the subjective units of distress assessment. If, after 2-sessions, the patient has subjective units of distress, related to the Intensive Care stay, at 0/10 (Peace, serenity, total relief) or 1/10 (No acute distress and feeling basically good), then the intervention will be complete and no more sessions are needed. This is consistent with the EMDR R-TEP protocol, developed by our trial group member. If the subjective units of distress are higher than 1 at the end of a session, the patient will be asked to come back again, repeating sessions, to a maximum of 8 or until they score 0/10 or 1/10.

If after 8-sessions of EMDR R-TEP, the patient is experiencing ongoing distress the therapy team will arrange an appropriate package of NHS care.

If at any time, other psychological issues arise or the patient exhibits signs of considerable distress, the therapy team, including the lead Consultant Clinical Psychologist, will arrange appropriate psychological care.

Please refer to appendices 1 and 2 for full details describing the EMDR R-TEP intervention, according to the Template for Intervention description and replication (TIDieR) checklist.[75.]

- 1. ***Assessments***

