These data will inform the design of a future randomised control trial , investigating the efficacy of an early EMDR R-TEP intervention in reducing psychological morbidity for Covid-19 related critical care survivors.

**Method:** Hospital-based research staff will approach consecutive eligible patients in hospital or within 12-weeks of hospital discharge to discuss the trial and to present the Patient Information Sheet. Consenting patients will complete baseline assessments, before random allocation to treatment or usual care. Patients in the intervention arm will be referred to an NHS psychological therapy service, whose staff are trained and experienced EMDR R-TEP practitioners. The psychological therapy service will arrange for an online, virtual baseline visit. There will be a minimum of 2 and a maximum of 8 sessions depending on patient need, assessed by the treating psychological practitioner, as per the EMDR R-TEP protocol. Each session lasts for 60-90 minutes. When the practitioner assesses that the patient is no longer experiencing disturbing thoughts or memories, the intervention will be complete.

The patient will be asked to repeat the assessments, 6-months following discharge from hospital. In addition, we will complete a post-study, process evaluation, consisting of semi-structured interviews with a representative sample of participants and staff.

**Outcomes:** Primary outcome will be feasibility and tolerability of the intervention. This will be assessed by recruitment rates and adherence to the EMDR R-TEP intervention and follow-up assessments.

Exploratory data of effectiveness will be collected by patient-reported questionnaire. We will assess PTSD symptoms using the PTSD CheckList – Civilian Version (PCL-C). We will assess anxiety and depression using the Hospital Anxiety and Depression Scale (HADS) and EuroQol Five Dimension- Five level scale (EQ5D-5L). The Montreal Cognitive Assessment (MOCA) tests cognitive ability. Patients will be asked to wear an activity monitor for 7-days. The Council of Nutrition Appetite Questionnaire (CNAQ) and Brief Resilience Scale (BRS) will also be completed at baseline and 6-months post-discharge.

The process evaluation will reveal themes that we will use to assess fidelity, quality and implementation.

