**Secondary outcome measures**

All secondary outcome measures will be collected at baseline and 6-months post-hospital discharge

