**Post-traumatic stress disorder:**

The PTSD Checklist-Civilian Version (PCL-C) is a validated, standardised self-reporting questionairre for PTSD comprising of 17 items that correspond to key PTSD symptoms[77]. Using a 5-point scale, participants are asked to indicate how much they have been bothered by these problems within the last month. (1= not at all; 5 = Extremely) PCL-C is rated by adding total scores.

**Anxiety and depression:** Hospital Anxiety and Depression Scale (HADS) is a 14-item, self-reported measure with 7-items relating to symptoms of anxiety and 7-items relating to depression[78]. Each item is scored from 0-3, providing categorical total scores for anxiety and depression. 0-7 = normal. 8-10 = borderline. 11-21 = abnormal.

**Cognitive function:** Montreal Cognitive Assessment (MoCA) is a validated tool, used to detect cogntive impairment[79]. MoCA is a 30-point test of short-term memory, visuospatial ability, executive function, attention, language, abstract reasoning and orientation. Scores range from 0-30. A score higher than 26 is considered to indicate normal cognitive function.

**Health Related Quality of Life:** EQ5D -5L comprises five quality-of-life dimensions; mobility, self-care, usual activities, pain/discomfort andanxiety/depression. Participants report levels ranging from ‘no problems’ to ‘extreme problems’.

**Resilience:** The Brief Resilience Scale is a validated measure of resilience. The capacity to recover from a traumatic event is dependent on mental processing of those trauma.

**Physical activity:** Patients will wear a wristband activity monitor following consent and at final assessment point, 6-months post-hospital discharge. The equipment has been validated for medical use and will be worn 24 hours per day for 7 consecutive days.

**Nutritional assessment:** The scored Council of Nutrition Appetite Questionnaire provides a validated assessment of appetite and predicted weight-loss and takes approximately 5-minutes to complete.

- 1. ***Additional data***

Hospital research staff will provide the following demographic and hospital admission information:

Age

Gender

Living arrangements

Postcode

Ethnicity

Employment status

Pre admission functional comorbidity index

ICU diagnosis

APACHE II score [81]

Duration of level 3 care

Duration of level 2 care

ICU and hospital length of stay

Days of ventilation

Sedation days

Episodes of delirium according to daily CAM-ICU measures[82]

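### First post-discharge contact and the EMDR start limit both close at week 12, so a patient contacted late can be randomised to therapy that cannot start on time

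*Protocol*

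**What the plan says.** **Approach.** The abstract states that research staff "will approach consecutive eligible patients in hospital or within 12-weeks of hospital discharge to discuss the trial". The recruitment and consent section (8.3) repeats the window and sets the rule for patients already at home: "If the patient has been discharged from hospital, within the last 12-weeks, research staff will make initial contact with a telephone call". After that call, an interested patient is sent the information sheet by post or email, a second call is arranged, and consent is documented.

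**Between consent and therapy.** The abstract fixes the order: "Consenting patients will complete baseline assessments, before random allocation to treatment or usual care". For patients allocated to EMDR and referred, "The psychological therapy service will arrange for an online, virtual baseline visit". The secondary outcomes section adds that "All secondary outcome measures will be collected at baseline and 6-months post-hospital discharge". Physical activity is one of these outcomes and appears in the baseline column of the schedule of events. For that outcome, "Patients will wear a wristband activity monitor following consent and at final assessment point", and the device "will be worn 24 hours per day for 7 consecutive days".

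**Start of therapy.** The primary aim, the abstract's aims, the lay summary, the intervention section (8.5) and the schedule of events all place the start of EMDR within 12 weeks of hospital discharge.

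**The concern.** Both limits run from hospital discharge and end on the same day, yet one event has to precede the other by several steps. A patient first telephoned near week 12 is validly approached under section 8.3. Once consented, that patient is to be randomised, and if allocated to EMDR cannot be seen by the deadline in section 8.5.

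The primary aim is whether therapy can be delivered starting within 12 weeks. A late start of this kind would be produced by the recruitment rule, but in the results it would look like a failure of the patient or the therapy service. Protocol adherence is a listed feasibility outcome, so it would count there. It would also be a deviation that section 11 requires to be reported to the sponsor at once. The 75% completion criterion does not mention the start date and is not directly affected.

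**Working it through.** The plan gives no figure of its own for this timing. Its one sample-size calculation reproduces (26 × (1 − 0.25) = 19.5, inside the stated 18–20 completers) but plays no part here.

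**Inputs from the protocol**
- Last permitted first contact: 12 weeks = 84 days after discharge (abstract; section 8.3).
- Last permitted first EMDR appointment: 84 days after discharge (primary aim; section 8.5).
- Baseline activity monitor: 7 days, worn after consent (secondary outcome measures).
- Baseline before allocation (abstract).
- Planned EMDR arm: 13 (lay summary).
- Time for the information sheet, second call and consent, and for referral and booking: not stated.

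**Formula.** Latest workable first contact = 84 − (information and consent + any baseline time before allocation + referral to first appointment).

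**Contact on the last permitted day.** Days left = 84 − 84 = 0. Any positive lag makes the start late.

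**Reading A: the monitor must finish before allocation.** This follows if the activity measure is one of the baseline assessments that precede allocation. With every other step taking no time, latest contact = 84 − 7 = day 77 (week 11). First contacts on days 78–84 cannot lead to an on-time start.

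**Reading B: the monitor may run past allocation.** Latest contact = 84 minus the time for the remaining steps, which the protocol does not give.

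**Range under assumed lags.** The assumptions are 1–7 days for information and consent, 0 or 7 days for baseline, and 0–14 days for referral.

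| Information and consent | Baseline | Referral | Total lag | Latest first contact | Share of the 84 days lost |
|---|---|---|---|---|---|
| 1 | 0 | 0 | 1 | day 83 | 1.2% |
| 1 | 7 | 0 | 8 | day 76 | 9.5% |
| 7 | 0 | 7 | 14 | day 70 | 16.7% |
| 7 | 7 | 14 | 28 | day 56 | 33.3% |

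Only the 7-day entry comes from the protocol. The last column is a share of calendar days, not of patients; the protocol does not say how many patients will be approached late.

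**Weight of one patient.** 1/13 = 7.7% of the EMDR arm.

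**Completion criterion.** 0.75 × 13 = 9.75, so 10 completers are needed (10/13 = 76.9%; 9/13 = 69.2%). Late starts would bear on this only if a late start counted as non-completion, which the protocol does not say.

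**Is there a rule that prevents it?** The eligibility criteria contain no limit on time since discharge. The capacity criterion includes being able to complete the interventions, but it sets no time limit. No readable text gives an earlier cut-off or a grace period. Figure 1 (patient flow) is not shown in the copy reviewed and could contain one.

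**The case against.** The strongest reply is that two shared outer limits do not contradict each other. Section 8.3 says when staff may call and section 8.5 says when therapy must begin, so sensible staff would let the tighter requirement govern and not randomise someone who can no longer be booked. That does not match the text: consecutive eligible patients are to be approached, and those who consent are to be randomly allocated. Nothing lets staff hold back a late patient.

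Other parts of the reply do stand:
- **Day 77 is conditional.** The device is only said to be worn after consent. The rule that baseline precedes allocation appears in the abstract and is not repeated in the randomisation section, and section 12 speaks of baseline questionnaire data. If the monitor may overrun allocation, the protocol yields no firm day.
- **The remaining lags can be short.** The sheet can be emailed, consent taken by telephone, randomisation is internet-based and therapy is online. The exposed period might be only a few days.
- **Few patients are likely to be exposed.** All patients are screened in the ICU, and many can be approached in hospital or soon after discharge. Those patients are unaffected.
- **A remedy has a cost.** An earlier cut-off could turn away patients who might have started promptly, in a single-centre trial of 26.

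These points limit the size of the problem; they do not remove it.

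**Conclusion.** The concern holds as a minor design fault. The contact window and the treatment-start window end on the same day although several sequential steps separate them, so the protocol followed as written can randomise a patient whose therapy cannot start within the period named in the primary aim.

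The size is bounded only in part. The last workable first contact is day 77 at best if the baseline monitor must finish before allocation; otherwise it is day 84 less an unstated lag. The number of patients cannot be derived and is probably small. The conclusion rests on the readable text and would soften if Figure 1 carries a cut-off, although sections 8.3 and 8.5 would then still need to agree with it.

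**What to change.** Keep the 12-week start limit, since it is the one in the primary aim, and change the recruitment rule in section 8.3 and the abstract in one of two ways.

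1. **Close first post-discharge contact earlier**, by the therapy service's actual time from contact to first appointment. If that lag were about 14 days (an assumption), the cut-off would be 84 − 14 = day 70, week 10. The cost is losing a few late-identified patients, some of whom might have started in time.
2. **Randomise only patients for whom a first appointment by week 12 is still possible.** This keeps late contacts who can be booked quickly. Patients approached but not randomised for this reason should be counted separately from the recruitment criterion (more than 30% of eligible patients approached), so that it is not distorted.

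Under either option, state whether the 7-day baseline monitor must finish before allocation. The change takes one or two sentences in section 8.3 and the matching line in the abstract.

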**Primary Outcome measure**

**Feasibility**

Hospital research staff will collect data on number of eligible patients from their ICU, number of eligible patients approached and number consented.

Therapy staff will collect data on adherence to the trial protocol and sessions attended.

Feasibility will be determined by:

- Recruitment of >30% of eligible patients approached
- Complete early EMDR intervention programme in 75% or more of trial participants
- Protocol adherence
- Incidence of attributable adverse events
- Outcome measures completed in 75% or more of trial participants

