| **Rationale** | A number of contemporaneous studies have reported Covid-19 related mental health issues. By 19^th^ June 2020 over 12,000 patients, with confirmed Covid-19, had been admitted to UK Intensive Care Units.  Patients who survive a period of critical illness have a disproportionately high chance of suffering from significant and persistant poor psychological outcomes.  Our study programme aims to investigate whether it is feasible to deliver an online Eye Movement Desensitisation Reprocessing (EMDR) intervention, delivered soon after hospital discharge and whether this intervention will improve psychological outcome for survivors of Covid-19 related critical illness. |
| **Study aims** | To evaluate the feasibility of delivering an online early EMDR protocol to patients who have survived Covid-19 related critical illness. |
| **Intervention** | Trial particpants, randomised to the intervention arm, will undertake an online psychological therapy EMDR Recent Tramatic Events Protocol (R-TEP).  This will consist of 2-8 personal sessions of EMDR R-TEP delivered by a suitably trained and experienced psychotherapist. |
| **Control arm** | Trial particpants randomised to the control arm will receive usual post-hospital discharge care. |
| **Feasibility outcomes** | 1. Able to recruit >30% of eligible patients approached 2. Complete early EMDR intervention programme in 75% or more of trial participants randomised to intervention. 3. Protocol adherence 4. Incidence of attributable adverse events 5. Outcome measures completed in 75% or more of trial participants |

1. **List of abbreviations**

| ASD | Acute Stress Disorder |
| --- | --- |
| BLS | Bilateral stimulation |
| BPS | British Psychological Society |
| BRS | Brief Resilience Scale |
| CBT | Cognitive Behavioural Therapy |
| CNAQ | Council on Nutrition Appetite Questionnaire |
| Covid-19 | Coronavirus Disease 2019 |
| EMDR | Eye Movement Desensitisation and Reprocessing |
| EQ5D-5L | EuroQol Five Dimension- Five level scale |
| HADS | Hospital Anxiety and Depression Scale |
| ICNARC | Intensive Care National Audit and Research Centre |
| ICU | Intensive Care Unit |
| IPTS | Intensive Psychology Therapy Services |
| MERS | Middle Eastern Respiratory Syndrome |
| MOCA | Montreal Cognitive Assessment |
| NHSx | National Health Service digital health and social care programme - |
| PCL-C | PTSD Checklist – Civilian Version |
| PCR | Polymerase Chain Reaction |
| PGH | Poole General Hospital |

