To ensure adherence with social distancing guidelines, our expert psychological therapy team have begun to deliver the EMDR therapy via online videoconferencing. This has been shown to be equally as effective as face-to-face sessions and is supported by the NHS technology arm, British Psychological Society and the American Psychiatric Association. The additional advantage is that ICU survivors will be spared a journey to a treatment centre and can undertake the therapy at home or the location of their choosing. Because we think that this is worthy of extra investigation, we aim to determine whether it is feasible to deliver online EMDR therapy to survivors of Covid-19 related critical illness and whether it might help to reduce psychological trauma associated with the illness and treatment.

A total of 26 survivors of intensive care, will be offered the EMDR therapy, in order to see whether they feel it is a good idea and whether they will volunteer to undertake sessions with a highly trained and experienced team of psychological therapists. These patients will be randomly placed into one of two groups.

In the ‘intervention group’, 13 patients will be referred to a local NHS community-based EMDR therapy team, run by expert Clinical Psychologists. They will attend between 2 and 8 online sessions, starting within 12-weeks of hospital discharge. We will ask our patients to complete some survey questionnaires, before and after therapy, to see whether it makes them feel better about their stressful experience. We will also record whether the patients completed the therapy and how they felt it might be improved or made more accessible.

In the ‘control group’, the remaining 13 patients will undertake all of the same questionnaires, but will not receive online EMDR. Patient’s final involvement will be to repeat the questionnaires 6-months after they have been discharged from hospital.

When the trial has been completed, we will ask to interview a number of trial participants and staff involved in the trial. The information that we gain from this study will be used to design a much larger study, which will investigate whether EMDR can be effective for all survivors of intensive care.

1. **Background and rationale**

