**Figure two: trial schedule of events**

^*^ Representative sample of particpants and staff

1. **Sample size**

This is a feasibility study, the results of which will be used to power a definitive study if appropriate. We anticipate a 25% mortality /loss to follow-up. A total of 26 patients will be recruited to this study, with estimated total of 18-20 patients completing the study.

1. **Process evaluation**

Qualitative, in-depth, semi-structured interviews will be conducted with patients enrolled in the trial and professionals involved in the delivery of the trial at completion. Patients from both arms of the study (up to 6) and professionals from participating sites (up to 6) will be interviewed. This will provide an opportunity for the research team to reflect on the experiences of patients and professionals, identifying barriers and facilitators to trial processes (professionals) and trial experiences (patients), in order to gain an in-depth understanding on process/relationships/communications that helped or hindered conduct of the trial.

Within the self-report questionnaire patients will be asked to indicate whether they can be contacted to participate in an interview. Interviews will be conducted by telephone. Interviews will be conducted by a researcher with experience in qualitative process evaluations. Encrypted audio recorders will be used.

1. **Safety considerations**

A number of systematic reviews have reported no adverse events attributable to EMDR (52-56). The intervention will be undertaken by suitably trained and experienced psychological practitioners from the NHS Intensive Psychology Therapy Service, Branksome Clinic in Poole. IPTS primarily provides a service to individuals with complex and severe, persistent psychopathologies. The service has an established and defined risk management and clinical governance structure.

All interventions will be delivered or supervised by [name], Consultant Clinical Psychologist, Head of Service and trial board member.

Online sessions will be compliant with Digital Approaches to therapy guidance from the British Psychological Society [72]and NHS Digital [74]. (These guidance contain expected standards relating to safeguarding, information governance, and GDPR.

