12. **When and how much**: The R-TEP intervention for this study is planned to take between 2-8 weekly sessions per participant. Each session will last 60-90 minutes. At 4-months post-hospital discharge all patients will be contacted via telephone, by NHS research nurses, in order to arrange a repeat of the baseline assessments completed following consent. Patients will be able to complete these assessment questionnaires by post or over the telephone.
13. **Tailoring**: The number of therapy sessions can vary on an individual basis depending on the participant’s severity of the identified trauma and how able they are to address it during treatment. This will be discussed with the treating clinician and mutually agreed prior to establishing the therapeutic framework of the intervention. Another aspect which can be tailored is whether the 3-month follow-up session is completed face-to-face or through telephone depending on the participant’s needs.
14. **Modifications**: None expected
15. **How well (planned)**: All clinicians who will deliver EMDR R-TEP in this study have been trained in the delivery of the intervention and will adhere to a standardised protocol of treatment. The number of therapy sessions can vary depending on each participant and this is an aspect of the study which can be difficult to control or plan in advance. We will be collecting adherence data as our primary outcome. These will inform the design of a future randomised controlled trial.
16. **How well (actual)**: to be reported following trial completion.

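### The therapy-completion criterion has two denominators; as worded in section 8.6 it cannot exceed 50% against a 75% threshold

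*Protocol*

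**What the plan says.** Section 8.6 of the protocol (Assessments, Primary Outcome measure) lists five items by which feasibility will be determined. Three carry a number: recruitment, therapy completion and completion of outcome measures. The therapy item reads "Complete early EMDR intervention programme in 75% or more of trial participants". The parallel list in the synopsis (section 1, Feasibility outcomes) reads "Complete early EMDR intervention programme in 75% or more of trial participants randomised to intervention".

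The lay summary gives the arm sizes. In the intervention group, "13 patients will be referred to a local NHS community-based EMDR therapy team"; in the control group, "the remaining 13 patients will undertake all of the same questionnaires, but will not receive online EMDR". Section 9 (Sample size) adds: "A total of 26 patients will be recruited to this study, with estimated total of 18-20 patients completing the study".

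The end of therapy is described in three places:

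- Abstract, Method: "When the practitioner assesses that the patient is no longer experiencing disturbing thoughts or memories, the intervention will be complete".
- Section 8.5 (Intervention): if the patient's distress score is 0 or 1 after two sessions, "then the intervention will be complete and no more sessions are needed"; otherwise sessions continue until that score is reached, up to a maximum of eight.
- Appendix 2, Tailoring: the number of sessions varies between patients and is to be "mutually agreed prior to establishing the therapeutic framework of the intervention".

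**The concern.** Half of the trial participants are never offered the therapy whose completion is being counted. A denominator that includes them puts a ceiling on the completion rate that has nothing to do with how well the therapy is delivered.

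Feasibility is the primary aim, and this is one of only three feasibility items with a numerical threshold. If two versions of it remain in the protocol, the same data can be reported as meeting or missing the criterion, and the choice between them could be made after the result is known.

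The surrounding text does not remove the doubt. In the same list in section 8.6, the phrase for trial participants is also the denominator for completing outcome measures, where it naturally means both arms. Some other sentences are loosely worded as if every consenting participant were referred for therapy, for example under Trial Design and setting and in the procedure item of Appendix 2.

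**Working it through.** **Inputs.** Total 26 (section 9). Intervention arm 13 and control arm 13, with no EMDR in the control arm (lay summary). Threshold 75% (section 8.6 and synopsis). Anticipated mortality or loss to follow-up 25% (section 9).

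**The plan's own figure.** Expected study completers = 26 × (1 − 0.25) = 19.5, which agrees with the stated 18 to 20. The sample-size statement is consistent and is not at issue here.

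**Section 8.6 wording (all trial participants).**

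- Highest attainable rate = intervention patients / all patients = 13/26 = 50.0%.
- Completers needed = 0.75 × 26 = 19.5, so 20. That is 7 more than the 13 patients offered EMDR.
- Taking only the expected study completers as the denominator, and supposing that all 13 intervention patients are among them and finish therapy, does not help: 13/20 = 65.0% and 13/18 = 72.2%, both below 75%.

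**Synopsis wording (randomised to intervention).**

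- Completers needed = 0.75 × 13 = 9.75, so 10.
- 10/13 = 76.9% passes; 9/13 = 69.2% fails; perfect delivery is 13/13 = 100%.

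**Where the two differ (arm of 13).**

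| Completers in the intervention arm | Section 8.6 | Synopsis |
| --- | --- | --- |
| 0 to 9 | fails | fails |
| 10 to 13 | fails | passes |

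**How likely a disagreement is.** The protocol gives no anticipated completion rate, so a range is assumed, with 13 independent patients. The chance of contradictory verdicts is the binomial probability of 10 or more completers:

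| Assumed completion probability | Chance that the two rules disagree |
| --- | --- |
| 0.60 | 17% |
| 0.70 | 42% |
| 0.75 | 58% |
| 0.80 | 75% |
| 0.90 | 97% |

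The better the therapy is delivered, the more likely the two statements are to conflict.

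**The end-of-therapy descriptions side by side.** The abstract relies on the practitioner's assessment and section 8.5 on a distress score recorded by the therapist. These can be read together, the abstract summarising the rule in section 8.5. Appendix 2 speaks of agreeing the number of sessions beforehand, which sits awkwardly beside a score-driven end, but it does not say that therapy is complete at that number. One case is left open: a patient who attends all eight sessions with a score above 1 has reached the maximum but not the condition that section 8.5 attaches to completion.

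**The case against.** The strongest reply is that nobody would apply the section 8.6 wording literally. Controls are never offered EMDR, so completing the programme can sensibly concern only those assigned to it, and the synopsis says so in an almost identical list. That largely stands. A reader might infer that the trial has set itself an impossible target, and the documents do not support this: the attainable denominator is already in the protocol, and section 8.6 most likely lost a few words. The protocol gives neither section precedence, so section 8.6 cannot be said to override the synopsis. Equally, the synopsis does not override section 8.6, and the contradiction remains.

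Two further inferences go too far. First, this is not a formal stop/go rule. The protocol says that feasibility will be determined by the five items, two of which have no threshold, and that the results will inform a later trial. Second, a reader might see three rival definitions of completion and conclude that the completion rate cannot be reproduced. The abstract can be read as a summary of section 8.5. The tailoring item defines no completion, and the same appendix says that session numbers are hard to plan in advance. What survives is a request for clarity.

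It is also fair to say that one patient separating a pass from a fail is a feature of any percentage threshold in an arm of 13. It is not counted as a defect here.

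**Conclusion.** The point holds as a contradiction between section 8.6 and the synopsis on the denominator of a primary feasibility criterion. On the section 8.6 wording the criterion is capped at 50% and cannot be met; on the synopsis wording it is met with 10 of 13. The verdicts conflict at 10 or more completers and agree at 9 or fewer.

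The figures rest on an exact 13/13 split, which appears only in the lay summary; section 8.4 names an internet-based randomisation system without giving block sizes or a ratio. A modest imbalance does not change the conclusion, because meeting the section 8.6 wording would need at least 20 of the 26 patients in the intervention arm, all of them completing. Under simple 1:1 randomisation (an assumption) that allocation has a probability of about 0.5%.

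The design, the sample size and the data to be collected are unaffected. The wording should still be corrected before results are assessed, because it fixes a primary threshold and the correction is free. The end-of-therapy descriptions are a minor, separate matter of consistency.

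**What to change.** In section 8.6, restrict the completion item to the intervention arm so that it matches the synopsis: "Complete early EMDR intervention programme in 75% or more of trial participants randomised to intervention". State that the denominator is everyone randomised to that arm. Keep the threshold as a percentage: it means 10 of 13 if the arm has exactly 13, but 9 of 12 (0.75 × 12 = 9) or 11 of 14 (0.75 × 14 = 10.5, rounded up) if allocation is uneven.

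As a minor addition, reconcile the abstract, section 8.5 and the tailoring item of Appendix 2, so that completion in the feasibility criterion points to one statement. That statement should also say whether a patient who attends all eight sessions with a distress score above 1 counts as having completed. Which clinical rule applies is for the investigators to settle; this review does not choose one.

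The cost is one phrase in section 8.6 and a cross-reference in the abstract and Appendix 2. Recruitment, therapy delivery and data collection do not change.
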